## **2.5 Risk benefit assessment**

Patients, who will enter this study, will benefit from a 50% chance to durably discontinue TKI therapy. TKI discontinuation itself is very safe. There is no risk of disease progression after TKI stop and no risk of failure to regain deep molecular remission, in the event of MMR loss. Restarting with the previous TKI will essentially always restore deep molecular remission. This evidence is based on large clinical study cohorts of more than 1.000 documented patients.

Secondly, IFN was the previous standard drug in CML. It is a safe drug and, as eluted in 2.2 and 2.4 has previously been shown - in uncontrolled studies - to enable induction of a durable TFR. It offers therefore a reasonable chance to increase the overall rate of TFR in CML patients.

Due to the longstanding experience with the therapeutic use of human IFN in the treatment of diverse malignancies (melanoma, lymphoma, CML) and infectious diseases (hepatitis C) IFN can be considered as a safe drug. Potential toxicities and side effects are well predictable and consist mainly of temporary flu-like symptoms. However, rarely, there are also significant side effects such as induction of auto-immune diseases (thyroiditis, vitiligo, sarcoidosis etc.). Hair loss, psychiatric symptoms and other auto-immune symptoms may also occur. All side effects can usually be controlled by dose reductions or treatment discontinuation. Toxicities require extremely rarely active treatment intervention.

This altogether suggests that benefits associated with a durable TKI discontinuation induced by AOP2014 by far outweigh potential risks associated with AOP2014 treatment. Any indication that AOP2014 maintenance, will negatively affect relapse rates or progression after TKI discontinuation cannot be identified, further underscoring the positive benefit/risk ratio.

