#### **12.1.5 Premature End-of-Treatment assessments**

Patients, who relapse **in arm A or arm B**, will resume TKI therapy and perform an early (premature) EOT visit. The molecular BCR-ABL RT-PCR (IS) follow up will then be performed and documented in the e-CRF (every 3 months after resuming the TKI as in surveillance phase until month 25 (see study flow chart 1.1 and Table 1 and Table 2).

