## 13 Discontinuation criteria

### 13.1 Withdrawal of patients from study treatment

All patients have the right to withdraw from the study at any time, for any reason, and without penalty or loss of benefits to which the patient is otherwise entitled. If the patient chooses to withdraw, the investigator must be informed immediately.

In case of premature end of the individual study therapy upon request of the patient, all efforts should be made to keep the patient in the study for follow-up. This is only possible if the subject will be informed verbally on the medically preferred option to still continue with the study surveillance procedures. The patient will then give his/her informed consent by means of a written, signed and dated consent form for the follow-up period. **The study visit(s) will then be continued according to protocol until the regular end of study (intention to treat).**

Reasons to prematurely discontinue study treatment in arm A or treatment free surveillance in comparator arm B **may** also be terminated by the investigator for one of the following reasons:

- Intolerable AEs / side effects of the study medication
- Severe (S)AE which make it necessary to stop study treatment permanently
- Abnormal laboratory value(s) which make it necessary to stop study treatment
- Non-compliance with the study protocol

Study treatment **must be** terminated for one of the following reasons:

- Pregnancy
- Reaching the primary endpoint, which is defined as an increase of the BCR-ABL level to > 0.1% (IS) at any time, corresponding to loss of MMR at any time
- Withdrawal of patient's consent to study treatment
- Study treatment termination by the investigator

**In case of molecular relapse (loss of MMR) or withdrawal of informed consent TKI treatment must be resumed immediately in arms A or B, irrespective of the phase of study.**

If the investigator terminates the treatment of patient prematurely, he has to inform the patient about his decision and has to record the primary reason for withdrawal in the patient file and to document the end of treatment in the e-CRF. Final study evaluations will be done according to the EOT visit. If the patient caused the premature withdrawal, all data before termination may be used for final analysis please also refer to 12.1.5 Premature End-of-Treatment assessments.

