### Primary efficacy endpoint

The four hypotheses will be tested in hierarchical order, see above. Null hypotheses 1, 2 and 4 will be tested with the two-sided, uncorrected chi-square test. Null hypothesis 3 will be tested with the two-sided log-rank test. The result of BCR-ABL ratio according to the IS needs to be observed. In case of null hypotheses 1, 2, and 4, the BCR-ABL ratio according to the IS has to be available. For the times 6, 12, and 24 months after stop of TKI (i.e. 7, 13, and 25 months after randomization), a time interval around the corresponding time is allowed. Each result should be relatable to exactly one of the visits scheduled in the protocol. Accordingly, intervals are defined by the time in the middle between two visits (schedule of visits see e.g. study flow chart). As visits are scheduled 6, 7, and 8 months after randomization, the interval for relating a result to the 7-month visit is given by 6.5 to 7.5 months after randomization. With visits planned 11, 13, and 15 months, the interval for relating a result to the 13-month visit is given by 12 to 14 months, and finally, with visits foreseen 24, 25, and 36 months after randomization, the result should be recorded within the interval from 24.5 to 30.5 months after randomization. In case of more than one observation within an interval, the approach of Pffirmann et al. will be chosen in order to determine the decisive result. In case of the observation of an extremely unfavourable result prior to the upper time limit of an interval, this result will be carried forward and will be rated as “no MMR/relapse”. Extremely unfavourable results are accelerated disease, blast crisis, or death from any cause. Details on the outcome will be reported. For analyzing null hypothesis 3, it is important to ensure that the BCR-ABL ratio is evaluated at all times foreseen in Table 1. Accelerated disease and blast crisis imply a prior loss of MMR. Molecular RFS probabilities over time will be described by Kaplan-Meier estimates. RFS probabilities over time will be compared by the log-rank test.

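### The fixed-time rule for H1, H2 and H4 does not carry forward an earlier loss of MMR, the event that defines relapse, and so conflicts with the endpoint definition

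*Protocol*

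**What the plan says.** Under Primary efficacy endpoint in section 16.7, the three chi-square tests need a PCR result: "In case of null hypotheses 1, 2, and 4, the BCR-ABL ratio according to the IS has to be available". Results are tied to visits by windows. For month 7, "the interval for relating a result to the 7-month visit is given by 6.5 to 7.5 months after randomization"; for month 13, "the interval for relating a result to the 13-month visit is given by 12 to 14 months"; for month 25, "the result should be recorded within the interval from 24.5 to 30.5 months after randomization". The one exception is that an extremely unfavourable result before the upper limit of a window is carried forward and rated as relapse. The section then defines that class: "Extremely unfavourable results are accelerated disease, blast crisis, or death from any cause".

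Other sections bear on the same patients:

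- **Relapse.** Section 4.1 defines it as any rise of BCR-ABL above 0.1% (IS). Section 13.1 says the primary endpoint is reached by such a rise, "corresponding to loss of MMR at any time". Section 16.4 runs time to relapse from randomization to loss of MMR or death.
- **After relapse.** Section 12.1.5 says that relapsing patients in either arm "will resume TKI therapy and perform an early (premature) EOT visit", with PCR every three months from then until month 25. Sections 12.1.4 and 13.1 make the TKI restart immediate and mandatory.
- **Expected course.** Section 2.5 states: "Restarting with the previous TKI will essentially always restore deep molecular remission". It gives no time course.
- **Drop-outs.** Section 16.7 rates a TKI restart as a drop-out for H1, H2 and H4 only when no loss of MMR came before it.

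**The concern.** The carry-forward list is worded as a definition, not as examples, and the endpoint event is missing from it. A programmer who follows that paragraph alone would classify a patient who lost MMR at month 4 by whatever PCR falls in the window, or would find none.

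This matters more than usual here, because the trial itself changes the relapser's later PCR values. Loss of MMR leads to TKI, and TKI is expected to bring BCR-ABL down again. A later in-window result then shows retreatment and not relapse-free survival. Arm B is expected to have more relapses, so misclassification would fall more heavily on arm B and pull the arms together. H1 is the primary test and opens the hierarchy. H3 uses time to first loss of MMR and is not directly affected, but section 16.1 allows it to be tested only if H1 and H2 are both rejected.

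**Working it through.** **1. The plan's own figures.** Inputs from section 16.10: RFS in arm B 55%, 50% and 45% at months 7, 13 and 25; arm A 20 points higher; two-sided 0.05; 80% power; uncorrected chi-square test; 10% drop-out.

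n per arm = [1.96·√(2p̄(1−p̄)) + 0.842·√(pA(1−pA) + pB(1−pB))]² / d²

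At month 25, p̄ = 0.55 and d = 0.20: [1.96·√0.495 + 0.842·√0.475]² / 0.04 = 95.9, so 96 per arm and 192 in total. Then 192/0.9 = 213.3, so 214. Power with 96 per arm is 83.3%, 81.2% and 80.0% at months 7, 13 and 25. All stated figures reproduce.

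**2. Where a relapser's PCR falls.** Assume PCR at exact three-month steps after the visit that detects relapse.

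- *Month-7 window (6.5–7.5).* Relapse at month 2 gives PCR at 5 and 8; month 3 at 6 and 9; month 4 at 7; month 5 at 8; month 6 at 9. Only month 4 lands in the window.
- There is one addition. A premature end-of-treatment visit, which includes PCR, is due at the latest by the next scheduled visit (section 12.1.4 and note 3 to the visit tables). A month-6 relapser may therefore also have a result near month 7.
- *Month-13 window (12–14).* Every relapse visit from month 2 to month 11 gives one PCR in the window. Those from months 2, 5, 8 and 11 fall exactly on the month-14 limit.
- *Month-25 window (24.5–30.5).* Every earlier relapse visit gives a result if the month-25 sample is taken or three-monthly PCR runs on past month 25.

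Under a literal reading, a missing result is thus the main risk at month 7, and scoring on an on-TKI result the main risk at months 13 and 25.

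**3. Sensitivity at month 7.** Assume 96 per arm, RFS 75% against 55%, and relapses spread evenly over the six visits at months 2 to 7. Relapsers: A 24 (4 per visit), B 43.2 (7.2 per visit). Let g be the share of month-4 relapsers back in MMR at month 7. Month-7 relapsers are scored as relapse.

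Without a month-6 end-of-treatment PCR in the window, relapsers from months 2, 3, 5 and 6 have no result: 16 in A and 28.8 in B. Evaluable: A 72 + 4 + 4 = 80; B 52.8 + 7.2 + 7.2 = 67.2. Apparent RFS: A (72 + 4g)/80; B (52.8 + 7.2g)/67.2.

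With that PCR in the window and still above 0.1% (assumption), evaluable numbers are 84 and 74.4.

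| Month-6 relapsers | g | A | B | Difference (points) | Power |
|---|---|---|---|---|---|
| no in-window result | 0 | 90.0% | 78.6% | 11.4 | 49% |
| no in-window result | 0.5 | 92.5% | 83.9% | 8.6 | 37% |
| no in-window result | 1 | 95.0% | 89.3% | 5.7 | 26% |
| scored as relapse | 0 | 85.7% | 71.0% | 14.7 | 62% |
| scored as relapse | 0.5 | 88.1% | 75.8% | 12.3 | 53% |
| scored as relapse | 1 | 90.5% | 80.6% | 9.8 | 43% |

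**4. Sensitivity at months 13 and 25.** Assume every relapser has an in-window result and a share r is back in MMR and scored relapse-free. Then p′ = p + r(1−p), and the difference becomes 20(1−r) points.

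| r | Difference (points) | Power, month 13 | Power, month 25 |
|---|---|---|---|
| 0 | 20 | 81% | 80% |
| 0.25 | 15 | 62% | 60% |
| 0.50 | 10 | 41% | 38% |
| 0.90 | 2 | 11% | 10% |

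The protocol gives neither g nor r.

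**5. With loss of MMR carried forward.** No relapser is lost or rescored, and the figures in step 1 return.

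**The case against.** The strongest reply is that the rest of the protocol already settles the matter. The hypotheses concern the probability of relapse-free survival, not MMR status on the day. Relapse is any loss of MMR, so a patient who lost MMR at month 4 cannot be relapse-free at month 7. The drop-out rule exempts a TKI restart that follows loss of MMR, which makes sense only if that patient already has an outcome. The sample-size section points the same way. It allows for 214 − 192 = 22 drop-outs, whereas the literal rule would lose a further 192 − 147.2 = 44.8 relapsers at month 7 (33.6 if month-6 relapsers have an in-window result). It also uses the same 45% as a time-to-event survival probability. On this view the list only adds outcomes that are not PCR values.

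Most of this stands as evidence of intent. A reader might infer that the plan instructs the analyst to count relapsers as relapse-free or to exclude them; no sentence says so, and the exclusion reading runs against the drop-out rule.

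It does not close the gap. The drop-out rule says who is not a drop-out, not how an earlier loss of MMR is scored at a fixed time. No sentence says that. If loss of MMR were already carried forward, listing accelerated disease and blast crisis would be largely redundant, since the same section says both imply a prior loss of MMR. Nor is this merely detail left to a SAP: the protocol fixes the rule itself, with a defined list, for confirmatory tests in a trial whose investigators are not blinded.

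**Conclusion.** The point holds as an incomplete derivation rule that contradicts the endpoint definition. Followed to the letter, it could misclassify earlier relapsers at all three chi-square tests, the primary one included. The direction of the effect is clear under the plan's own assumption of more relapses in arm B: the planned 20-point difference shrinks.

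The size is not known. Month-7 power of about 26–53% (50–100% of month-4 relapsers recovered) or 49–62% (none recovered) rests on an even spread of relapses, exact three-month PCR steps, and whether the premature end-of-treatment PCR falls in the window. The figures for months 13 and 25 rest on assumed recovery shares; section 2.5 supports recovery in the end but not by any given month. A reader might conclude that the trial is underpowered or that its treatment difference will collapse. The documents do not support that: the sample size is correct for the endpoint as defined, and these losses arise only if the rule is applied literally.

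**What to change.** In section 16.7, under Primary efficacy endpoint, add any BCR-ABL (IS) value above 0.1% at or before the upper limit of the interval to the results that are carried forward. State that such a patient is rated as no MMR/relapse at that time point and all later ones, whatever a later PCR shows and whether or not one exists. Require an in-window PCR only from patients with no earlier event.

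The cost is a sentence or two in the protocol and the matching derivation in the SAP. No new data or visits are needed, and 192 evaluable and 214 randomized patients remain right. The change should be in place before H1 is tested at the first interim analysis (section 16.8).

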## 16 Statistical Considerations

### 16.1 Hypotheses

Four hypotheses are tested in hierarchical order. To avoid inflation of type 1 error (false rejection of a null hypothesis), further confirmatory testing has to be stopped as soon as a null hypothesis could not be rejected. All four hypotheses are tested at significance level 0.05.

At first,

Null hypothesis 1: “The probability of molecular relapse-free survival (RFS) 7 months after randomization / 6 months after stopping TKI is not different between the two arms A and B”

is tested against the

Alternative hypothesis 1: “The probability of molecular RFS 7 months after randomization / 6 months after stopping TKI is different between the two arms A and B”.

In case null hypothesis 1 can be rejected,

Null hypothesis 2: “The probability of molecular RFS 13 months after randomization / 12 months after stopping TKI is not different between the two arms A and B”

is tested against the

Alternative hypothesis 2: “The probability of molecular RFS 13 months after randomization / 12 months after stopping TKI is different between the two arms A and B”.

In case null hypothesis 2 can be rejected,

Null hypothesis 3: “No difference in the molecular RFS probabilities between the two arms A and B at any time”

is tested against the

Alternative hypothesis 3: “Molecular RFS probabilities between the two arms A and B are different”.

In case null hypothesis 3 can be rejected,

Null hypothesis 4: “The probability of molecular RFS 25 months after randomization / 24 months after stopping TKI is not different between the two arms A and B”

is tested against the

Alternative hypothesis 4: “The probability of molecular RFS 25 months after randomization / 24 months after stopping TKI is different between the two arms A and B”.

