## 16.2 Analysis Populations

### Definitions of Analysis Populations

|                                     |                                                                                                                                                                                            |
|-------------------------------------|--------------------------------------------------------------------------------------------------------------------------------------------------------------------------------------------|
| Intention-to-treat (ITT) population | All randomized patients                                                                                                                                                                    |
| Safety population                   | All randomized patients who receive at least one dose of treatment in Arm A or attended at Visit 1 in Arm B. The safety population will be used for the analyses of all safety parameters. |
| Per-protocol (PP) population        | All patients in the ITT population for whom no major protocol violations/deviations occurred                                                                                               |

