## 16.7 Methods of Analysis

The analyses of the primary and secondary efficacy endpoints will be performed for the ITT population. All randomized patients will be analysed within the group they were randomized to, not regarding their actual further treatment. In addition, the confirmatory analysis of the primary endpoint will be performed for the PP population as sensitivity analysis.

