Allogeneic stem cell transplantation in chronic phase or restart of TKI after prior stopping of TKI and without prior loss of MMR will be rated as a drop-out in case this happened prior to an evaluation which would be needed to determine the result for an interval corresponding to hypothesis 1, 2, or 4. In case of hypothesis 3, the observation time of a patient is censored at the time of allogeneic stem cell transplantation or of a restart of TKI without a prior loss of MMR. In this case, the censoring means a loss of information reducing the precision of the estimated probabilities of molecular relapse-free survival but should not alter the estimated probabilities themselves. Accordingly, it is important that the reasons for the reintroduction be clearly stated in any case. Estimated with the Kaplan-Meier method, the probabilities of molecular relapse-free survival describe what to expect, what can be really achieved, if the possibility of a premature TKI restart would not exist.

In case the event “restart of TKI without a prior loss of MMR” has to be regarded as informative with respect to the probabilities of molecular relapse-free survival, the Kaplan-Meier method is not

appropriate. Instead, the cumulative probabilities of a molecular relapse over time have to be estimated by the cumulative incidence function (CIF) 60. The event “restart of TKI without a prior loss of MMR” is then regarded as a competing risk.

Whatever the situation, non-informative or informative censoring, the cumulative incidence function will be calculated (in addition). It will present the cumulative probabilities of a molecular relapse under consideration of the presence of the competing event “restart of TKI without a prior loss of MMR” and also provide an estimation of the probabilities of this competing event itself.

Differences between the treatment strategies prior to discontinuation will be tested by the Gray test (Gray RJ et al., Ann Stat, 1988), if the assumption of non-informative censoring does not hold.

As explorative analyses, depending on the endpoint, multivariate logistic or Cox regression analyses will be performed to analyse the influence of baseline covariates such as the effect of different duration of prior TKI therapy.

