## 16.10 Sample Size Calculation

Molecular relapse-free survival (RFS) will be tested at three fixed times, 7, 13, and 25 months after randomization. In arm B, without any treatment after stopping TKI, the probabilities of molecular RFS at 7, 13, and 25 months are assumed to be 55%, 50%, and 45%. At each time, an increase by an absolute value of 20% in arm A is expected. At all three times, confirmatory testing is intended. To avoid an inflation of type I error, the hypotheses are put in hierarchical order. At all times, a power of 80% is planned. It is a characteristic of the binomial distribution that the variance is the higher, the nearer the probabilities are to the level of 50%. Accordingly, sample size estimation needs to be based on the assumptions at 25 months.

Patients in the standard arm B are expected to have a molecular relapse-free survival probability of 45% 24 months after discontinuation of TKI treatment. In the investigational arm A, we expect that the molecular RFS probability after 24 months of discontinuation of TKI can be increased by 20% as compared with the standard arm. Accordingly, 192 patients need to be randomized 1:1 to be able to reject the null hypothesis of same relapse-free survival probabilities with a two-sided uncorrected chi-square test at a significance level of 0.05 and a power of 80%. With an expected drop-out of 10%, the 1:1 randomization of 214 patients is necessary. The sample size calculation was performed with the program “PS Power and Sample Size Calculations”, Version 3.1.2 (Dupont WD et al., Controlled Clin Trials, 1997).

The hierarchical ordering of the hypotheses will be in accordance with the chronological ordering of the times. Assuming that all drop-outs will occur before 6 months (the most adverse case), 192 patients would be ready for analysis. With these 192 patients randomized 1:1, a molecular RFS probability of 55% at 7 months in arm B and of 75% in arm A, we would be able to reject the null hypothesis of same relapse-free survival probabilities with a two-sided uncorrected chi-square test at a significance level of 0.05 with a power of 83%.

With 192 patients randomized 1:1, a molecular RFS probability of 50% at 13 months in arm B and of 70% in arm A, we would be able to reject the null hypothesis of same relapse-free survival probabilities with a two-sided uncorrected chi-square test at a significance level of 0.05 with a power of 81%.

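### Hypotheses 1, 2 and 4 drop patients who restart TKI without losing MMR, against the stated ITT rule; the comparison is distorted when restart differs by arm or is informative

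*Protocol*

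**What the plan says.** The ITT population in section 16.2 is "All randomized patients", and the opening of section 16.7 applies it to the efficacy endpoints: "All randomized patients will be analysed within the group they were randomized to, not regarding their actual further treatment".

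Under the primary endpoint, the same section says "Null hypotheses 1, 2 and 4 will be tested with the two-sided, uncorrected chi-square test" and adds a condition: "In case of null hypotheses 1, 2, and 4, the BCR-ABL ratio according to the IS has to be available". It then states that a patient still in MMR who has a chronic-phase allogeneic transplant or restarts TKI "will be rated as a drop-out in case this happened prior to an evaluation which would be needed to determine the result" (again, hypotheses 1, 2 and 4). For hypothesis 3, the log-rank test, the same patients are censored at the restart or transplant.

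Section 16.10 shows what drop-out means for the denominator: "Assuming that all drop-outs will occur before 6 months (the most adverse case), 192 patients would be ready for analysis". The number randomized is 214.

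The one sensitivity analysis named for the primary endpoint is the per-protocol population.

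**The concern.** A patient's later treatment decides whether that patient is counted, which the ITT sentence rules out. This is not a detail left open for the SAP: the protocol fixes the rule, and an SAP that follows it inherits the conflict.

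The rule also acts unevenly on outcomes. A patient who relapses before a would-be restart stays in as a failure. A patient who restarts while relapse-free is deleted and can no longer count as a success. The observed proportion is therefore too low even if restart has nothing to do with relapse risk. Section 16.7 argues that censoring costs only precision, but that argument concerns the Kaplan-Meier analysis for hypothesis 3. It does not carry over to a proportion with the restarters removed.

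Hypothesis 1 is the primary test and gates the other three. The trial is open-label and only arm A receives interferon, so restart rates could well differ between arms.

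**Working it through.** **The plan's own figures.** Inputs from section 16.10: 45% vs 65% at 25 months, two-sided 5% level, 80% power.

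n per arm = [1.96·√(2·0.55·0.45) + 0.8416·√(0.45·0.55 + 0.65·0.35)]² / 0.20² = (1.379 + 0.580)² / 0.04 ≈ 95.9, so 96 per arm and 192 in all. Then 192 / 0.90 = 213.3, so 214. With 96 per arm, power is 83.3% (55% vs 75%), 81.2% (50% vs 70%) and 80.0% (45% vs 65%). The stated figures reproduce. With 107 per arm and no restarts, power at month 7 is 87.1%.

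**Non-informative restart, month 7.** The protocol gives a total drop-out of 10% and no restart rate by arm, so the rates below are assumptions. Relapse and restart have independent constant hazards; x is the share of the arm that restarts relapse-free. The chi-square then sees

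P(neither relapse nor restart) / (1 − x).

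- Arm B, true 55%: x = 5% gives 51.4/95 = 54.1%; x = 10% gives 47.7/90 = 53.0%; x = 20% gives 40.6/80 = 50.8%.
- Arm A, true 75%: x = 10% gives 66.4/90 = 73.8%; x = 15% gives 62.1/85 = 73.1%; x = 20% gives 57.8/80 = 72.3%.

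| Restart B / A | Observed B / A | Difference (true 20.0) | Power | Type I error if both arms are truly 55% |
|---|---|---|---|---|
| 0% / 0% | 55.0% / 75.0% | 20.0 | 87.1% | 5.0% |
| 10% / 10% | 53.0% / 73.8% | 20.7 | 85.3% | 5.0% |
| 5% / 15% | 54.1% / 73.1% | 19.0 | 78.5% | 6.0% |
| 0% / 20% | 55.0% / 72.3% | 17.3 | 69.9% | 9.0% |

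With more restart in A, the bias runs against A. With 20% in B and none in A it runs the other way: 50.8% vs 75.0%, a difference of 24.2 points.

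**Against Kaplan-Meier at month 7.** Simulation with 107 per arm, restart spread uniformly over months 1 to 7, and a complementary log-log comparison:

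- 10% in each arm: power about 85% to 86% by either method.
- 15% in A, 5% in B: power 80% (chi-square) against 85% (Kaplan-Meier).
- 20% in A, 5% in B: power about 75% against 84%; type I error about 6.2% against 4.8% (repeat runs: 6.2% to 6.6% against 4.8% to 5.2%).

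**Informative restart.** Suppose 10% of arm B restart just before they would have relapsed.

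- Chi-square: 55/90 = 61.1% instead of 55%.
- Kaplan-Meier with censoring: 10 of the 45 points of relapse are hidden, so the hazard falls by the factor 35/45, and 0.55^(35/45) ≈ 63%.
- Restart counted as failure: 45% fail either way, so arm B reads 55%.

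With 107 in A and 96 left in B, power is about 57% for the chi-square and 47% for Kaplan-Meier.

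**Price of counting restart as failure when restart is non-informative.** At 10% in each arm: 47.7% vs 66.4%, power 79.1%. At 5% in B and 15% in A: 51.4% vs 62.1%, power about 35%.

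**The case against.** Section 16.7 is not blind to restart. It requires reasons for restart to be recorded, plans a cumulative incidence function with restart as a competing event in every case, and adds Gray's test if censoring is informative. These would expose an imbalance between arms. They are time-to-event tools, however, and none changes the tests of hypotheses 1, 2 and 4.

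The size depends on assumed rates. With equal restart and no true difference there is no between-arm bias and type I error is kept. At 15% vs 5%, power is still close to the planned 80%. This stands. A reader might infer that the rule biases the comparison whenever anyone restarts; the arithmetic does not support that.

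A reader might also infer that Kaplan-Meier censoring alone solves the problem, or cite the power loss under informative restart in its favour. Neither holds: in that case censoring does worse than the chi-square, and the protocol itself calls Kaplan-Meier unsuitable when restart is informative.

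Nor do the documents promise full follow-up of all 214. Under sections 13.1 and 19.3, follow-up after a patient ends therapy early needs fresh written consent, and full withdrawal loses the later outcome under any rule. Finally, aiming at RFS as if premature restart could not happen is a legitimate choice of target. It still does not justify deleting restarters from a proportion.

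**Conclusion.** The contradiction is plain on the text: the ITT rule and the drop-out rule cannot both govern hypotheses 1, 2 and 4, and no stated analysis of those tests keeps the restarters. The sample size itself is consistent with its inputs.

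The bias is real but conditional. Within an arm, non-informative restart of 5% to 20% lowers the observed RFS by about 1 to 3 points in most settings; the largest case worked here is 4.2 points (20% restart, true 55%). Between arms it matters when restart is unequal: at 20% in A and 5% in B, power is about 75% against 84% and type I error about 6.2% against 4.8%. Because the bias there runs against A, the extra false rejections tend to favour B. Informative restart distorts more, and in either direction.

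All of this rests on assumed restart rates and timing. The change should be made because hypothesis 1 gates the confirmatory sequence and the repair is cheap.

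**What to change.** Reconcile the two statements in section 16.7 before the month-7 analysis:

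1. Analyse hypotheses 1, 2 and 4 in all 214 randomized patients, each contributing follow-up until relapse, censoring or the time point. Compare Kaplan-Meier RFS at 7, 13 and 25 months (complementary log-log scale, Greenwood variance), with restart or transplant without loss of MMR censored as already done for hypothesis 3.
2. Pre-specify alongside it an all-randomized analysis that counts restart or transplant without loss of MMR as failure. This covers informative restart and matches the aim in section 2.4 of more patients stopping TKI for good.
3. Keep the complete-case chi-square as supportive.
4. Report the restart rate by arm from the cumulative incidence function already planned.

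The cost is analysis wording only, with no new data or patients. The fixed-time test is slightly less familiar than a chi-square. The restart-as-failure analysis gives lower RFS and can lose much power if restarts fall mainly in arm A, so its role relative to the first analysis must be stated in advance.
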